**Conclusions:**

The C3Link Program is expected to yield better screening and follow-up outcomes than the control but will require more resources. Incremental cost-effectiveness of each strategy in the outlined sequence will be determined.

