For the community setting, there is growing evidence on the important role CHWs play in addressing individual and interpersonal barriers to improve knowledge and encourage women to seek medical care [12,13,33,37]. In Kenya, pilot studies in Meru and Nyeri counties have shown that CHWs can facilitate uptake of cancer screening [14,31]. We will use the lessons learned to develop 2 packages of strategies, the C3Link Core and C3Link Plus models. For C3Link Core, CHWs will deliver group education sessions to women and families (male partner or other support person), which is an evidence-based, low-cost strategy to promote cancer screening [15,16,34,35,38]. In our formative research, we found that many women were comfortable discussing issues related to fear and misinformation in individual rather than group settings [19-21]. Therefore, we hypothesize that group education sessions will motivate some women to screen, but others will require an individual-level strategy, or a combination of multiple individual-level strategies [39], to seek screening. To optimize available resources and adopt a tiered process through which only women who require multiple strategies are offered them, C3Link Plus will include the C3Link group education sessions and then add on individual evidence-based strategies [40-42] that increase in resource intensity in a sequential order, targeting women who remain unscreened at 1-month intervals. Women who remain unscreened after group sessions will first receive one-on-one education, followed by motivational interviewing, and, finally, navigation to address specific barriers.

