Preimplementation phase for planning (6 months)		
Community—train CHWs^b^	13 basic modules plus 6 modules of study-specific content	No study CHWs
Clinic—strengthen quality, referrals, and provider interactions	Readiness assessment; standard procedures, diagnosis triage; training on high-quality screening and documentation	Readiness assessment; standard procedures, diagnosis triage; training on high-quality screening and documentation
Intervention phase to test multicomponent strategies (24 months implementation and follow-up)		
Community— Increase women’s knowledge, self-efficacy, care-seeking behavior, and social support (reduce stigma) Deliver individual strategies that increase in intensity to women who need additional support (C3Link Plus only)	C3Link CHW-led education sessions (each community): Three-weekly women’s club meetings with education modules Six group sessions for family members or support persons	Awareness campaign in the community using flyers developed and provided by the National Cancer Institute of Kenya
Community— Increase women’s knowledge, self-efficacy, care-seeking behavior, and social support (reduce stigma) Deliver individual strategies that increase in intensity to women who need additional support (C3Link Plus only)	C3Link Plus only—focus on care-seeking behavior: Level 1: women not screened at 9 months will receive one-on-one education, level 2: women not screened at 10 months will receive individual counseling through motivational interviewing, and level 3: women not screened at 11 months will receive navigation to address barriers	Awareness campaign in the community using flyers developed and provided by the National Cancer Institute of Kenya
Clinic— Embed study CHWs so that, with their support, results and referrals are conveyed Improve the quality of screening	Practice facilitation with community linkages (each clinic) Monthly case review meetings with study CHWs and PDSA^c^ cycles with clinic teams led by clinic champions	Those who visit clinics may benefit from improvements, but there are no community–clinic linkages with CHWs
Maintenance phase to test reduced level of support (additional 24 months for a total of 36 months of follow-up)		
Community—provide support to maintain behavior change	Quarterly women’s club meetings Two group sessions for family members or support persons	Awareness campaign continues

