### Data Analysis

Hypothesis testing will be carried out by intent to treat, and we will examine the effects at the individual level across the 3 randomization groups. We will use generalized estimating equation models to estimate the effects of the randomization groups. If the Hausman assumption of correlation between the random and fixed effects is violated, then we will include fixed effects representing cluster identification [71]. We will adjust for baseline covariates, including sociodemographic and behavioral factors, should the initial descriptive analyses suggest differences in the distribution of these factors across study randomization groups. We will also explore the use of propensity scores to control for systematic differences between the groups. In further analyses, we will compare differences in mediating outcomes across the groups and examine the potential moderating roles of key individual behavioral, social, and structural factors hypothesized to influence cancer screening and adherence along the cancer care continuum, as shown in Figure 1. We will test the “dose” of the C3Link Core and Plus strategies received as a covariate in these models. We will explore differences in breast and cervical cancer screening completion and report the proportion that complete at least one of the screenings. As appropriate, we will perform analyses separately or pooled together for the younger and older cohorts of women to assess whether care-seeking behavior differs by age group. A key aspect of interest in this study is the extent to which perceived and anticipated stigma affects care-seeking behavior and screening completion. In subsequent analyses, we will consider both medium-term outcomes within the first 12 months after enrollment and changes at any point during the 24-month and 36-month follow-up period to assess longer-term outcomes. To understand potential variation across communities, we will conduct comparisons to analyze differences in mediating and screening outcomes among each of the C3Link Core and Plus communities. We will also report on the overall quality of the screenings provided, women’s preferences for cervical cancer screening, and the type of procedures used along the continuum of care. For the C3Link Plus arm, we will document the increase in screening completion with each step in the series of individual strategies and the number of women requiring each type of strategy.

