Although cluster randomization reduces contamination across study arms, it increases the risk that women in each arm may differ at baseline. This study’s sampling frame will allow us to assess baseline differences before randomization and adjust our sampling process with propensity score weighting methods. Second, data could be missing because of nonresponse and study attrition. This study’s CHWs in each community will maintain regular contact with the women, and we will also use rigorous field data collection practices, including training data collectors, developing protocols, and monitoring fidelity continually. To limit missing data, we will train clinic staff and data collectors and implement continuous quality review. Furthermore, we will address any missing data by including demographic covariates that will serve as proxies for dropout and conducting sensitivity analyses.

We will select 1 eligible woman from within each household in the selected communities. To reduce interviewer bias, we will use the Kish method to provide a random and consistent procedure for women’s selection.

A key constraint in implementing strategies in low- and middle-income countries is funding. This is the first cancer screening study in Kenya, and to our knowledge, in any other limited-resource setting, that will evaluate implementation strategies in a predetermined sequence and assess effectiveness and cost at each step. This will allow us to determine the incremental cost-effectiveness of each strategy in the sequence to guide policy. For example, given the available resources and cost-effectiveness profile, a Kenyan county may decide to implement C3Link Core with only the first level in the sequence of C3Link Plus. Importantly, the findings will guide future studies in testing additional combinations and sequences.

This trial features novel evidence-based strategies to increase uptake of breast and cervical cancer screening in variously resourced settings in a cost-effective process. We anticipate that the findings will be valuable not only in Kenya but also in other sub-Saharan African countries.

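### The article promises the incremental cost-effectiveness of each Plus step, but one-month escalation and the three-arm design leave the 24-month result of Core plus level 1 alone unobserved

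*Protocol article*

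**What the plan says.** The claim appears twice. The Abstract (Conclusions) says: "Incremental cost-effectiveness of each strategy in the outlined sequence will be determined". The Discussion (Defining Features of our Approach) repeats it as a guide to policy: "This will allow us to determine the incremental cost-effectiveness of each strategy in the sequence to guide policy". It then gives an example: "a Kenyan county may decide to implement C3Link Core with only the first level in the sequence of C3Link Plus".

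The schedule is fixed in Table 1 (Implementation Strategies): "women not screened at 9 months will receive one-on-one education", then "women not screened at 10 months will receive individual counseling through motivational interviewing", then navigation for those unscreened at 11 months. The Objectives describe the same rule as "targeting women who remain unscreened at 1-month intervals". The section on the Plus sequence of personalised strategies counts a woman as unscreened until both the breast and the cervical screening are complete.

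Recruitment lists three arms: Core, Plus and enhanced standard of care. For the steps, Data Analysis says that in the Plus arm "we will document the increase in screening completion with each step in the series of individual strategies" and that the number of women needing each strategy will be counted. The short-term economic analysis is a comparison across trial arms using cost per woman screened. The primary end point is at 24 months.

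**The concern.** A cost-effectiveness ratio for one step needs the extra women screened because of that step, compared with the same programme without it. Here each step is followed within a month by the next, for every woman who still needs it. The option that the Discussion offers to counties, Core plus level 1 and nothing further, is not given to any group to 24 months.

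The step analysis is also confined to Plus. A within-arm count after each step includes women who would have been screened that month anyway, and women responding late to an earlier step. Because both screenings must be complete before a woman leaves the sequence, some late completion is plausible. Counties could fund or drop a step on figures that partly reflect timing. The primary comparison between arms is not affected.

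**Working it through.** **1. What the plan sizes.** The article gives no figure for a single step. Its power statement concerns whole arms and reproduces for 15% versus 30%. With 9 communities of 80 women after 20% attrition, the effective size per arm is 720/(1 + 79 × ICC), which is 213.6 at ICC 0.03 and 145.5 at ICC 0.05. Power by the two-sided normal test at 0.05 is 0.963 and 0.869, consistent with the stated figure of over 80%.

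**2. Observation time (from Table 1 and the 24-month end point).** From month 9 to month 24 there are 15 months.

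| Latest step received | Months | Share |
|---|---|---|
| Level 1 | 9–10 (1 month) | 1/15 = 7% |
| Level 2 | 10–11 (1 month) | 1/15 = 7% |
| Level 3 | 11–24 (13 months) | 13/15 = 87% |

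**3. What randomisation identifies.** Core and Plus share the same programme up to month 9. Given dated screenings in both arms:
- Plus minus Core at month 10 gives the one-month effect of offering level 1.
- Plus minus Core at month 11 gives the cumulative effect of levels 1 and 2.
- Plus minus Core at any later time gives the effect of the whole sequence.

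The change in the difference between months 10 and 11 is not a pure level-2 effect, because it includes late level-1 responses.

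**4. Background screening.** Suppose no step works and screening runs at a constant monthly rate (assumption). At the plan's control uptake, h = 1 − 0.85^(1/24) = 0.00675. At its Core uptake, h = 1 − 0.70^(1/24) = 0.01475. Women unscreened at month 9 at the Core pace: 900 × (1 − 0.01475)^9 = 787. In months 9–10, 10–11 and 11–12 the within-Plus counts are then about 5, 5 and 5 at the control pace, or 12, 11 and 11 at the Core pace. All would appear as step increments unless Core screening is subtracted.

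**5. Carry-over.** The article gives no response delay. Assume an exponential delay with mean d months. The share of level-1 responders completing after level 2 has begun is e^(−1/d): 14% (d = 0.5), 37% (1), 61% (2), 72% (3). The shares falling in months 9–10, 10–11 and after 11 are 63/23/14% (d = 1), 39/24/37% (d = 2) and 28/20/51% (d = 3).

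**6. Effect on step increments.** These are simulated cases with no background uptake, each screening credited to the latest step received, and follow-up to month 24. Values are percentage points for levels 1/2/3. True means the 24-month gain from adding each level to those before it.

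| True response per level | Mean delay | True | Credited |
|---|---|---|---|
| 20% each | 0.25 month | 20.0/16.0/12.8 | 19.6/16.0/13.1 |
| 20% each | 1 month | 20.0/16.0/12.8 | 12.7/15.2/21.0 |
| 20% each | 2 months | 20.0/16.0/12.8 | 7.8/11.7/29.3 |
| 30% level 1 only | 1 month | 30/0/0 | 18.9/6.9/4.1 |

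The distortion is negligible with a very short delay. It reverses the order in the second and third rows and keeps level 1 first in the fourth. The crediting rule, the window and the delay decide which applies, and the article states none of them.

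**The case against.** The strongest reply is that the formal economic analysis is across arms, that the county example is only illustrative, and that the article says its findings will guide later studies of other combinations. Attribution windows are also detail that an article can leave to the full protocol or analysis plan. This answers any complaint that a crediting rule is missing. It does not answer the main point: no crediting rule can supply the 24-month result of Core plus level 1 without assumptions, and the article says the ratio for each strategy will be determined.

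Three stronger readings are tempting, and the documents do not support them.
- **That no step's effect is observed at all.** Plus versus Core at month 10 is a randomised contrast for level 1 over one month.
- **That navigation will look many times more effective even if nothing works.** Crediting it with everything to month 24 gives about 65 null screens at the control pace, against 5 for each earlier level. That compares 13 months with 1 month, a comparison the article nowhere states. To month 12 the null counts are about 5, 5 and 5.
- **That the last step is necessarily favoured.** This depends on the crediting rule and the delay. Navigation also goes to women who did not complete screening after two earlier steps. If they are harder to reach, that works against it, and the simulated cases do not model this selection.

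**Conclusion.** The concern holds as a claim that goes beyond the design. The 24-month yield and cost per woman screened of Core plus level 1 are not observed, because escalation occurs at one month and no arm stops at level 1 or 2. This conclusion rests on the schedule and the list of arms, not on any assumed rate.

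The step analysis, as described, mixes step effects with background screening and carry-over. The illustrative sizes are about 5 to 12 background screens per one-month window, and 14% to 72% of level-1 responses falling after level 2 begins. They assume a constant screening pace and an exponential delay with a mean of 0.5 to 3 months. Neither the size nor the direction of the net distortion can be fixed from the article. The Core versus full Plus comparison stands.

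**What to change.** - In the Abstract conclusions and the Discussion, limit the randomised cost-effectiveness claim to Core versus the full Plus sequence.
- Report step yields over equal one-month windows (months 9–10, 10–11, 11–12) as cumulative Plus-minus-Core differences at months 10, 11 and 12, using dated clinic-audit screenings in both arms.
- Label the separate level 2 and level 3 increments as descriptive, because of carry-over and selection by earlier response.
- Show months 12–24 only for the whole sequence.
- Present any first-level-only cost-effectiveness as a modelled scenario, with a stated carry-over assumption and a sensitivity range.

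This changes wording and analysis only, with no change to the intervention schedule. It needs no new data if the clinic audits record screening dates in Core as well as Plus, which should be confirmed. The price is a weaker step-by-step message to policymakers.

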### Conclusions

The C3Link Program is expected to yield better screening and follow-up outcomes than the control (the enhanced usual care), but will require more resources.
